### *Remote vs In-Person Care Analysis*

During our prior RCT of home hospital, patients experienced a mean of 0.09 (SD 0.29) adverse events during their home hospital admission. We believe the smallest clinically meaningful treatment difference would be 0.1 adverse events (i.e., from 0.09 to 0.19 adverse events per patient). In this non-inferiority trial ( $\alpha=0.025$ , power 80%, non-inferiority limit 0.1 events), we would require 210 patients (105 in each arm). Because of clustering, the actual required sample size will be larger. With 5 home hospital physicians ( $\rho$  0.01), we require 260 patients (130 in each arm). We consistently enroll 25 patients monthly, leaving us with sufficient power after about 11 months.

We plan an interim futility analysis. After 130 patients have completed the remote vs in-person care study, we will calculate the difference in adverse event rates between the two arms. If the difference is 0.10 or higher (with the higher rate in the intervention arm), then we will stop the trial for futility. This rule will reduce the power about 2%.

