### Safety monitoring

If any of the following concerning safety events occur, a blinded monitoring committee will review the event to determine attribution to the intervention: fall, medication error, DVT/PE, mortality during admission, transfer back to hospital (committee cannot be blinded for this endpoint). If any of these events are felt to be due to the home hospital intervention, they will be reported to the IRB with recommendations for appropriate actions to be taken. Decisions to modify the protocol or suspend the study will be made jointly by the study investigators, monitoring committee, and the IRB.

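### The interim futility rule costs well under 1 point of power, not about 2%, and stops only about half of trials at the excess the protocol calls clinically meaningful

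*Protocol*

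**What the plan says.** All the figures are in the Protocol, Power analysis, Remote vs In-Person Care Analysis. In the earlier randomized trial "patients experienced a mean of 0.09 (SD 0.29) adverse events during their home hospital admission". The smallest meaningful change is given as "from 0.09 to 0.19 adverse events per patient". The design uses alpha 0.025, sidedness not stated, with "power 80%, non-inferiority limit 0.1 events". Without clustering, "we would require 210 patients (105 in each arm"); with five physicians and an intraclass correlation of 0.01, "we require 260 patients (130 in each arm").

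The interim look comes after 130 patients have completed the comparison. The rule is: "If the difference is 0.10 or higher (with the higher rate in the intervention arm), then we will stop the trial for futility". Its cost is given in one sentence: "This rule will reduce the power about 2"%. The protocol does not say how often the rule would stop the trial, either when the arms are equal or when remote care is worse.

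The Safety monitoring section adds committee review of listed events, without numeric thresholds: "Decisions to modify the protocol or suspend the study will be made jointly by the study investigators, monitoring committee, and the IRB".

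**The concern.** The power cost is the only operating characteristic given for the only numeric rule that compares the arms. A reader told that the rule costs about 2% of power will take it to be a moderately demanding brake. But the rule acts only once the observed excess has reached the whole non-inferiority margin. A trial in that position at the halfway point usually fails at the end with or without the rule, so the rule should take away very little power. For the same reason it should stop rather seldom when remote care really is worse by the margin. If so, the stated cost gives the wrong impression of what the rule does.

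**Working it through.** **Inputs.** SD 0.29, margin 0.10, final size 130 or 105 per arm, and the threshold 0.10 come from the protocol. Assumptions: 1:1 allocation, hence 65 per arm at the look; alpha 0.025 read as one-sided, with 0.05 as a variant; approximate normality, checked by simulation.

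**1. Reproducing the sample size.** n per arm = 2 × 0.29² × (z for alpha + z for power)² / 0.10².
- One-sided 0.025: 2 × 0.0841 × (1.960 + 0.842)² / 0.01 = 132.02, so 133 per arm.
- One-sided 0.05: 2 × 0.0841 × (1.645 + 0.842)² / 0.01 = 103.99, so 104 (105 with a t-based calculation).

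The stated 105 per arm therefore reproduces only at one-sided 0.05. With 130 / 5 = 26 patients per physician per arm, the design effect is 1 + 25 × 0.01 = 1.25, and 210 × 1.25 = 262.5, close to the stated 260. Both alpha readings are carried below.

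**2. Chance of stopping when the arms are equal.** Interim standard error = 0.29 × √(2/65) = 0.0509. P(observed excess ≥ 0.10) = P(Z ≥ 0.10/0.0509 = 1.966) = 2.5%. Exact counts give 2.3% (binomial) and 2.9% (Poisson). With design effect 1.25 the standard error is 0.0569 and the chance is 3.9%.

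**3. Power actually lost.** Power is lost only when the trial crosses the threshold at the look and would have succeeded at the end. At 130 per arm and one-sided 0.025, the final standard error is 0.29 × √(2/130) = 0.0360. Success then needs an observed difference below 0.10 − 1.96 × 0.0360 = 0.0295. The interim and final differences have correlation √(65/130) = 0.707. The bivariate normal probability of both events at a true difference of 0 is the loss:

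| Final n per arm | One-sided alpha | Design effect | Power without rule | Power lost (points) |
|---|---|---|---|---|
| 130 | 0.025 | 1 | 79.4% | 0.32 |
| 130 | 0.025 | 1.25 | 70.1% | 0.35 |
| 130 | 0.05 | 1 | 87.2% | 0.60 |
| 130 | 0.05 | 1.25 | 80.0% | 0.71 |
| 105 | 0.025 | 1 | 70.5% | 0.06 |
| 105 | 0.05 | 1 | 80.3% | 0.17 |

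Simulation at 130 per arm and one-sided 0.025 gives 0.27 (Poisson) and 0.28 (binomial). Across all variants tried, including SD 0.30 and other design effects, the loss lies between about 0.04 and 0.8 points. Reading the 2% as relative does not help: 2% of 80% is 1.6 points.

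**4. Where 2% may come from.** It is close to the stopping chance in step 2. That chance is an upper bound on the loss, not the loss: at 130 per arm and one-sided 0.025, only 0.32 / 2.47 = 13% of the trials stopped under equality would have succeeded. At one-sided 0.05 the share is 18% with the design effect and 24% without.

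**5. Chance of stopping when remote care is worse.** At true rates 0.09 and 0.19 the threshold equals the true difference, so the chance is 50% (exact Poisson 49.4%, binomial 49.8%). At an exact doubling, 0.09 and 0.18, it is about 43%.

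**6. Thresholds that would cost 2 points.** At 130 per arm and no design effect, the threshold is 0.072 at one-sided 0.025 (stops 71% at a true excess of 0.10) and 0.081 at one-sided 0.05 (stops 65%).

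**The case against.** The strongest reply is that this is a small, conservative slip. The protocol overstates the cost of its own rule by about 1.3 to 1.7 points; the sample size, margin, alpha and final inference are untouched; and an approximate 2% is close to a valid upper bound. All of that stands. It limits the weight of the point but does not make the sentence correct.

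Several stronger readings are tempting, and the documents do not support them.
- **That the rule is weaker against harm than promised.** The protocol promises no stopping probability under harm and labels the rule futility. The 50% follows directly from setting the threshold equal to the margin.
- **That the rule is the only protection.** It is the only numeric rule comparing the arms, but Safety monitoring gives a discretionary route to suspension, Outcomes monitoring adds daily and weekly review, and physicians may see remote-arm patients in person.
- **That an interim excess of 0.07 to 0.09 is already a lost trial.** At one-sided 0.025 and 130 per arm, conditional power there is 5.6% down to 0.9% if the observed trend continues, but 41% down to 27% if the arms are truly equal.
- **That the threshold ought to be 0.07.** In the setting that reproduces 260 patients, 0.07 would cost about 3.5 points and stop 10.9% of trials with equal arms. The choice is open.
- **That the treating team will see the interim difference, or that the rule conflicts with Safety monitoring.** The protocol's use of the first person does not say who handles the data. A prespecified futility rule can coexist with a joint decision after event review, and such conduct may be set out elsewhere.

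**Conclusion.** The stated power cost is wrong as written. The loss is about 0.3 points at one-sided 0.025 and about 0.6 to 0.7 points at one-sided 0.05, and no variant reaches 2. The rule would stop about 2.5 to 4% of trials with equal arms and about 50% of trials at an excess of 0.10, so it gives limited protection as the only numeric comparison of the arms.

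This rests on SD 0.29, 65 per arm at the look and an approximately normal difference. The exact loss depends on the alpha sidedness and design effect, which the protocol leaves unclear; the conclusion that it is under 1 point does not. The correction is worth making because a stated operating characteristic should match its rule, not because the trial's inference is at risk.

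**What to change.** In Remote vs In-Person Care Analysis, replace the 2% sentence with three statements:
- the power loss is under 1 point (about 0.3 at one-sided 0.025, or about 0.7 at one-sided 0.05 with clustering), naming the alpha sidedness and design effect used;
- the chance of stopping when the arms are equal is about 2.5 to 4%;
- the chance of stopping at a true excess of 0.10 is about 50%.

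This is a change of wording and leaves the sample size, alpha, margin and stopping threshold as they are.

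Optionally, if the sponsor does mean to spend about 2 points of power, re-derive the threshold once sidedness and design effect are settled. At 130 per arm it would be about 0.07 at one-sided 0.025 or about 0.08 at one-sided 0.05. The price is more stopping when the arms are equal: about 7.8% and 5.6% respectively without a design effect, against 2.5% now. The documents require no particular threshold.

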### *Early Transfer*

To calculate sample size, we used simulation in the PASS program (NCSS LLC, Kaysville, UT) comparing gamma distributed costs, with baseline data based on the home hospital RCT. With 324 patients in each arm of the study, even accounting for intraclass correlation by Home Hospital physician (intraclass correlation coefficient 0.01, cluster size 65), we will have 82% power to detect a relative decrease of 21% in total costs of care, smaller than the 27% decrease seen in this outcome in the Home Hospital RCT and close to the smallest reduction that would be considered clinically important. This sample size will also provide 80% power to detect a 43% reduction in readmission (again smaller than that seen in the Home Hospital RCT), and 81% power to detect non-inferiority for adverse events (assuming a baseline of 0.15 events per patient).

**Paramedic Analysis**

Similar power calculations as those in the standard home hospital and remote vs in-person care analysis apply.

## RISKS AND DISCOMFORTS

### Uncommon: Complications of surgical and non-surgical procedures

Standard hospital procedures carry small risks and discomforts. For example, venipuncture can be painful and can lead to thrombophlebitis, but this is uncommon and readily rectifiable.

### Uncommon: Device complications/malfunctions

IV pumps, vital signs monitoring patches, and the other devices used during home hospital uncommonly have malfunctions.

### Uncommon: Radiation risks

Patients can receive radiography while admitted to home hospital, much the same as when they are admitted in the hospital. We do not anticipate that home hospital will in any way change the prevailing risk of radiation.

### Common (but unchanged from usual care): Drug side effects and toxicities

Drug side effects and toxicities do occur during inpatient medicine, despite following best practices and evidence based medicine. We do not anticipate that home hospital will in any way change the prevailing rate of drug side effects and toxicities compared to usual care. For example, acute kidney injury can occur in patients receiving antibiotics, even when correct dosing occurs. Home hospital is equipped to monitor and respond to the common drug side effects and toxicities much the same as the standard of care (monitoring, diagnostics, fluids, etc).

### Common (but improved from usual care): Psychosocial risks

Admission to the hospital can be a psychosocially difficult event, particularly for a senior. We believe home hospital will alleviate these typical risks. Home hospital is equipped to assist patients with psychosocial stressors through improved staffing ratios and a social worker.

## POTENTIAL BENEFITS

### Potential benefits to participating individuals

- Remain in their home despite acute illness
  - Eat their own culturally concordant food
  - Sleep in familiar surroundings
  - Maximize time and interactions with their family and friends
- Improved health outcomes (we anticipate these from previous literature)
  - Reduced length of stay
  - Reduced complications while admitted

- Less delirium
  - Fewer falls
  - Fewer health care associated infections
  - Decreases reduction in functional status
- Improved patient experience
- Clinical improvements to the standard of care
  - Point of care blood diagnostics (results at the bedside in <5 minutes);
  - Minimally invasive continuous vital signs, telemetry, and activity tracking, including clinical deterioration algorithms, steps taken, and sleep quality;
  - On-demand 24/7 clinician virtual video visits;
  - 12 to 1 patient to MD ratio, compared to typical 16 to 1;
  - Ambulatory/portable infusion pumps that can be worn on the hip;
  - Optional access to a personal home health aide, community health worker, and community paramedic
- Improved transitions of care
  - Ability to coach patients on their post-discharge care plan in the appropriate environment, with caregivers available, and with adequate time for teaching given provider to patient ratio

### Potential benefits to society

- New evidence-based care paradigm for acute care hospitalization.
- Lower total medical expenditure. Allows for redirection of resources to areas in need.
- Might eventually lead to reduction in total hospitals in the U.S.
- Provide needed randomized controlled data on the home hospital intervention to inform payment methods moving forward.

## MONITORING AND QUALITY ASSURANCE

### Independent monitoring of source data

The study's research assistant will collect all data denoted above. The PI and co-PI will monitor the source data throughout the project.

### Safety monitoring

If any of the following concerning safety events occur, a blinded monitoring committee will review the event to determine attribution to the intervention: fall, medication error, DVT/PE, mortality during admission, transfer back to hospital (committee cannot be blinded for this endpoint). If any of these events are felt to be due to the home hospital intervention, they will be reported to the IRB with recommendations for appropriate actions to be taken. Decisions to modify the protocol or suspend the study will be made jointly by the study investigators, monitoring committee, and the IRB.

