### Rationale

Our encouraging outcomes, coupled with the hospital's ongoing capacity concerns, led the hospital to require a single-arm intervention-only home hospital study for our current slate of included conditions that began in January, 2018. We have enrolled over 300 patients since January, 2018 very successfully and have consistently presented our safety data for the Committee's review. With our present local

data, compounded by the plethora of international studies cited above, we believe we have shown that home hospitalization delivers a reasonable substitute to hospitalization for correctly selected patients.

We seek to continue and expand this work in the context of IRB approval for several reasons, including the continued ability to

- employ devices in off-label uses. For example, the IRB previously approved the use of a wireless patch to record and report on vital signs. We continue to benefit from use of this device. We seek to deploy additional technologies to the home, all described below.
- deploy novel personnel. For example, the IRB previously approved the use of paramedics in our home hospital team. We intend to continue our use of paramedics, described below, and test in a retrospective pre/post design the impact of our already-deployed home hospital paramedic on safety and patient experience.
- Prospectively collect and report on a battery of outcomes, many of which are first-in-class and will benefit from additional sample size. For example, the IRB previously approved collection of daily steps.
- Test remote physician care. In a randomized controlled non-inferiority trial, we will test an in-person daily physician visit (“in-person care;” control) vs a daily physician visit conducted remotely via video facilitated by a care team member (“remote care;” intervention) for patients who are home hospitalized. For patients in the remote care arm, the physician can pragmatically choose to see a patient in-person based on the clinical context.

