### *Remote vs In-Person Physician Care*

In a randomized controlled non-inferiority trial, we will test an in-person daily physician visit (“in-person care;” control) vs a daily physician visit conducted remotely via video facilitated by a care team member (“remote care;” intervention) for acutely ill patients who are home hospitalized. The primary outcome (dependent variable) is number of adverse events during the acute episode of care (see “Summarizing Adverse Events” table below). The primary predictor (independent variable) is study arm (in-person care vs remote care). We will assess the non-inferiority of the primary outcome with a generalized linear model using Poisson distribution, given the primary outcome is count data. Although we have multiple covariates of interest, we are cognizant of over adjustment. We plan to adjust for age, gender, race/ethnicity, PRISMA-7, education, and HOSPITAL score). We may include additional covariates if groups have significant differences at baseline.

Because patients in the intervention arm will receive at least some of their intervention through a “change agent” (in this case, a Home Hospital team) shared with other participants, we need to account for this in the analysis. We will therefore cluster by Home Hospital physician using general estimating equations.

Other outcomes will be analyzed in a similar manner, using Poisson regression for other “count” outcomes (e.g., number of new or worsening signs or symptoms per patient, days at home since discharge), multivariable logistic regression for binary outcomes (e.g., 30-day readmission, ED visit, PCP

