### Outcomes monitoring

The physician and RNs will daily review quality and safety data as part of a rapid logistics improvement process.

Weekly, all physicians and RNs will huddle to review quality and safety data as part of a rapid logistics improvement process.

At 3 weeks into the home hospital clinical service, a blinded monitoring committee will review outcomes data and make recommendations to the study team.

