### **Adverse event reporting guidelines**

All adverse events denoted above under safety monitoring will be reported to the monitoring committee.

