## APPENDIX

### Selected Safety data to-date

|                                              | n (%)        |
|----------------------------------------------|--------------|
| Adverse Event a                   | Home (n=203) |
| 30-day unplanned readmission                 | 15 (7)       |
| Transfer back to hospital                    | 5 (2)        |
| Delirium                                     | 5 (2)        |
| New DVT/PE                                   | 0            |
| New pressure ulcer                           | 2 (1)        |
| Thrombophlebitis at peripheral IV site       | 4 (2)        |
| Catheter-associated urinary tract infection  | 0            |
| New Clostridium difficile                    | 0            |
| New MRSA                                     | 0            |
| New arrhythmia in heart failure b | 0            |
| Mortality during hospitalization             | 0            |

a None of these adverse events were deemed secondary to the intervention.

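### The monitoring committee's remit was not updated for the remote versus in-person RCT, so no independent body is assigned a by-arm review of harm

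*Protocol*

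**What the plan says.** Under Safety monitoring, the Protocol names the events that a blinded committee reviews for attribution: "fall, medication error, DVT/PE, mortality during admission, transfer back to hospital (committee cannot be blinded for this endpoint". The reporting rule follows: "If any of these events are felt to be due to the home hospital intervention, they will be reported to the IRB". Adverse event reporting guidelines ties what the committee receives to that same list: "All adverse events denoted above under safety monitoring will be reported to the monitoring committee".

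Outcomes monitoring sets one dated committee review: "At 3 weeks into the home hospital clinical service, a blinded monitoring committee will review outcomes data". It also has the treating physicians and nurses look at quality and safety data daily and weekly.

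The Rationale describes a "single-arm intervention-only home hospital study for our current slate of included conditions that began in January, 2018" and adds: "We have enrolled over 300 patients since January, 2018 very successfully". Treatment Assignment introduces randomization to remote or in-person physician care as an amendment to that running protocol. For this RCT, the section Remote vs In-Person Physician Care states: "The primary outcome (dependent variable) is number of adverse events during the acute episode of care". It refers to the 14 items in the table Summarizing Adverse Events.

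The power section for the same RCT plans one interim look. After 130 patients the study team compares adverse event rates between arms and stops for futility if the remote arm is higher by 0.10 or more.

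**The concern.** Adverse events are the primary outcome of the RCT, and the open question is whether a remote physician visit causes more of them. The monitoring section does not follow that question. Its event list, its causal question and its one dated review all fit a comparison of home with hospital, and none has been adapted to two arms that are both treated at home.

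Followed as written, an excess of delirium or acute kidney injury in the remote arm would not be sent to the committee. It would not trigger an IRB report under the Safety monitoring rule, and it would meet no dated committee review during the RCT. The one planned comparison by arm would be made by the people running the trial.

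**Working it through.** **1. Event list against primary outcome.** The 14 items in Summarizing Adverse Events, set against the five committee events:

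- On both lists (4): fall; VTE (DVT/PE on the committee list); transfer back to hospital; mortality during admission.
- In the outcome but not on the committee list (10): delirium, pressure ulcer, thrombophlebitis, CAUTI, C. difficile, MRSA, arrhythmia, hypokalemia, acute kidney injury, 30-day mortality.
- On the committee list only (1): medication error, which is in none of the data-collection tables.

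Coverage is 4/14 = 29%, so 10/14 = 71% lies outside. If 30-day mortality is set aside because the outcome is defined over the acute episode, 9 of 13 items still lie outside.

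**2. Illustration from the Protocol's own data.** Selected Safety data to-date (203 home patients) shows, readmissions aside, 5 transfers, 5 delirium, 2 pressure ulcers and 4 thrombophlebitis: 5 + 5 + 2 + 4 = 16. Only the transfers are on the committee list: 5/16 = 31%. Falls and medication errors are not tabulated there, so this is an illustration and not an estimate; any such event would raise the share.

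**3. Causal question.** In Treatment Assignment the RCT intervention is remote care and the control is in-person care. Every RCT patient receives home hospital care, so attribution to home hospital cannot separate the arms. The blinding exception has the same source. A transfer back reveals that a patient was at home rather than in hospital, but not whether the physician visit was remote. The Safety data table likewise marks transfer back as collected in the intervention arm only, which makes sense only for home versus hospital.

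**4. Timing.** The single-arm phase began in January 2018 and had passed 300 patients before the RCT was added by amendment. Three weeks into the service is therefore, on the natural reading, before the RCT. If it were instead three weeks into the RCT, at 25 patients a month: 25 × 21/30.4 ≈ 17 patients, and 17 × 0.09 ≈ 1.6 events.

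**5. The by-arm look that does exist.** Inputs from the power section: SD 0.29, 65 patients per arm, stop at a difference of 0.10 or more, stated power cost about 2%.

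- Standard error at the look: 0.29 × √(2/65) = 0.0509.
- With no true difference, P(stop) = 1 − Φ(0.10/0.0509) = 2.5%, or 2.9% by Poisson simulation at 0.09 events per patient. This caps the power loss; simulating two stages of 65 per arm gives a loss of 0.3 to 0.6 points. The stated 2% is within 2 points of this and is not at issue.
- P(stop) by true excess in the remote arm (normal approximation; Poisson simulation in brackets): 0.05, 16% (20%); 0.10, the margin itself, 50% (49%); 0.15, 84% (76%).
- The look falls at 130/25 = 5.2 months of a 260/25 = 10.4 month accrual.

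**6. Workload of a full review.** 0.09 × 260 = 23.4 events. If the remote arm ran at the margin: 130 × 0.09 + 130 × 0.19 = 36.4.

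**The case against.** A reader might infer that nobody is assigned to see excess harm in the remote arm, that the unlisted events are never reviewed, or that the three-week review is the committee's only one. The Protocol does not support any of these. The 130-patient look is a by-arm comparison of the primary outcome with an action threshold, and delirium and kidney injury count in it. Clinicians review safety data daily and weekly. The committee also reviews listed events as they occur, throughout the study. A footnote to the safety table says that none of the tabulated events, including delirium and thrombophlebitis, was judged to be due to the intervention, so somebody did assess attribution for events outside the list. The footnote does not say who.

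Nor is home versus hospital a superseded comparison. It is still the primary aim and a current row of the Study endpoints table. The home-hospital attribution question and the transfer-back blinding exception still serve it.

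Two further points have force. Safety monitoring first speaks of attribution to the intervention in general, which could cover remote care; only the IRB-reporting sentence narrows it to home hospital. And adjudicating a selected set of events one by one is a defensible choice, because a composite outcome does not require individual adjudication of every hypokalemia.

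What remains is narrower. The clinician reviews are not stated to be by arm, the 130-patient look is not given to the committee, and the reporting trigger does not ask about the treatment that is randomized.

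**Conclusion.** The point holds as a failure to update the monitoring section for the RCT. The committee list covers 4 of the 14 primary-outcome items. The IRB trigger asks about a treatment that both arms receive. The only dated committee review very probably fell before randomization began. That last point is an inference, since the Protocol gives no start date for the clinical service, but the alternative reading would yield only one or two events.

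A by-arm look exists, so the gap is one of independence and remit and not an absence of any comparison. The look is made once, by the study team, under a futility label, and would stop the trial about half the time if the true excess equalled the 0.10 margin. That figure assumes equal arms of 65, the stated SD or Poisson counts, and no clustering. No independent body is assigned a by-arm review of harm. The section should be corrected; this does not show that harm would go wholly unseen.

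**What to change.** Reconcile Safety monitoring, Outcomes monitoring and Adverse event reporting guidelines with the RCT's outcome definition and interim plan:

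- **Attribution.** For RCT patients, add to the IRB-reporting question whether the event is attributable to the remote or in-person physician-visit model. Keep the home-hospital question and the transfer-back blinding exception for the home versus hospital studies.
- **Scheduled review.** Replace the three-week review with committee reviews of all events in Summarizing Adverse Events, tabulated by coded arm, at set RCT enrolment counts. Make the existing 130-patient look one of them. Tabulation is enough; individual adjudication of every minor event is not needed.
- **Medication error.** Either add it to the Safety data table or state how it is to reach the committee.

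The cost is a wording amendment and one or two extra meetings of an existing committee, to review about 23 expected events. Coded arms preserve its blinding.
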